***Data source 6: Proxy Measurements of “Male Involvement”***

In order for outreach staff to contact study participants for missed visits or STI treatment, all MIRA participants are asked to provide permission and details to be contacted at their home, through their spouse’s work, through a rural address or a through another contact. Exiting MIRA study participants complete a “Permission to Contact Form” described above, which captures permission for women or their partners to be contacted post-study participation. The number of women consenting to partner contact will be tabulated and analysed as a proxy measure of “male involvement”.

**Quantitative Data Analysis Plan**

The following is a summary of the quantitative data analysis plan, including a discussion of statistical considerations, broken down by study aim.

**Frequency and Degree of Male Involvement**

There is no standardized way of measuring male involvement, therefore a necessary first step of the analysis is to further define what male involvement is. This will be explored by tabulating the frequency and degree of male involvement reported by female participants on the Male Partner Involvement Form. These will be descriptive statistics of the proportion of female participants, together with 95% confidence intervals, who report that her partner is supportive, aware of her study participation, like the products, participate in the use of products, etc. Social science data will be coded for descriptions of what male involvement is in women’s own words, including evidence of high vs. low and negative/positive involvement. This should help to expand upon, corroborate and clarify the quantitative data. Service statistics and proxy measures of male involvement (described above) will also be tabulated to contribute to this analysis. These statistics will capture which male partners have come to the clinics, and which services, i.e. counselling, treatment, testing, they have accessed.

Salient features of “male involvement” should emerge from this exercise, such that key variables representing higher vs. lower or positive vs. negative “male involvement” may become evident. Composite variables may be constructed that incorporate more than one binary outcome. These variables will be considered as independent predictors in further analysis of acceptability, adherence and biological outcomes. These measures are not pre-constructed, and have not yet been formally validated. In the analysis process, tests of construct validity will be done, whereby individual questions are correlated with hypothesized outcomes in order to gauge their validity.

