**RESEARCH PROTOCOL**

**Study Aims**

The overall goal of this study is to measure and describe the effect of male involvement on women’s adherence to (i.e. uptake of) male condoms[[6]](#footnote-4) and female-controlled methods of HIV/ STI prevention. “Male involvement” encompasses the actions, preferences and attitudes of the primary male partner. The objectives of the study are below. In the data analysis section of this document there is a more in-depth description of how each aim will be addressed analytically.

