**Data collection methods and activities**

***Data source 1: The Male Partner Involvement Form (MPIF)***

The major source of “male involvement” variables that will be used for exploring the domain of “male involvement”, and correlating male involvement with adherence, acceptability and other demographic, behavioural and clinical data are from the Male Partner Involvement Form.

This questionnaire is administered to female study participants of the Zimbabwe MIRA site (n=2500) at Months 3 and 12. The form has 58 questions. Approximately half of the responses have dichotomous yes/no responses, and the other half have continuous scales. Five items have specify lines for greater open-ended detail, e.g. “Have you invited him to come for free HIV and STI testing? If no why not (specify)________________”.

The aim of the questionnaire is to measure women’s perception of the quantity and quality of her partner’s involvement in study participation and study product use. The form attempts to explore the domains of partner communication, participation and control, and male partner’s attitudes and support for condom, diaphragm and gel use. Questionnaire items were constructed from a variety of sources, including the parent study instruments, previous qualitative studies done in Zimbabwe and other parts of southern Africa, and anecdotal discussions during pilot testing with male Zimbabwean research staff.79-84

The Male Partner Involvement Form was translated and back-translated into Shona from the English, and is interviewer-administered by female (to match respondents) study staff in either language, although the vast majority are in Shona (~99%). Interviewers hold tertiary-level degrees, and have a minimum of 3 years of interviewing experience. Interviewers receive extensive protocol training, form-specific training, and sign-off on SOPs which outline the intention item-by-item, of each question on each form in the study. Data will be double-entered into an Access database, and exported into SAS for analysis.

Table 1 below summarizes the anticipated sample size and the data collection points for this portion of the study, accounting for women who had already passed the first and second data collection points for the Male Involvement Study at the time of implementation.

***Table 1. Expected sample size for Male Partner Involvement Form, by study and data collection time point, (December 2004 – September 2006)***

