***Data source 2: Existing data about male partners and female product adherence and acceptability***

In addition to the new data specifically being collected for the Male Involvement Study, data are being collected on male partners through Audio Computer-Assisted Self-Interview (ACASI) interviews and on Case Record Forms (CRFs) as part of the main clinical trial. For example, partner’s age, employment, migration, marital status, multiple partnerships, use of alcohol/drugs and violent behaviour. Questions also cover some aspects of product use disclosure and clandestine use, relationship control and decision-making. Questions about product acceptability contain partner factors in the list of potential responses women can choose.

The primary outcomes of the Male Involvement Study - women’s adherence and acceptability - will be measured from data collected in the main study, as will the HIV/STI incidence data for the secondary objective analysis. Study product adherence is notoriously difficult to measure, as it relies on self-report and is subject to several potential sources of bias, most notably social desirability and recall bias. In an attempt to minimize the former, the MIRA study uses ACASI interviews, mentioned above, which seek to encourage greater honesty (and minimize data processing error) by direct entry of potentially sensitive responses into a computer. To address the latter challenge of recall bias, participants are asked about use of each study product for three different time periods: last act of sex, sex in the past week, and sex in the past three months. Although these time periods all have strengths and limitations, triaging recall periods should contribute to an understanding of the reliability and validity of the measures.

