**Primary Study Aim 1: The effect of male involvement on women’s adherence to condoms, diaphragm and gel.**

The association between the degree of male involvement and adherence will be examined by the development of a categorical scale for *reported* adherence level to each study product (diaphragm, gel, condoms) during sex. Analysis of adherence will be stratified by study arm as this might confound degree of male involvement (i.e. women in condoms arm are more likely to have discussed study products with partner since he is more involved in using them). It is possible that this association may be confounded, i.e. male involvement may be lower in couples with ‘limited’ education and those with ‘limited’ education may have the lowest adherence, resulting in a spurious association between male involvement and adherence. In order to account for this, and other potentially confounding variables, a multivariate analysis will be conducted using a multiple logistic regression model in the SAS statistical package.

Focus groups and in-depth interviews with men and women may give additional insight into the association between male involvement and adherence. As described above, qualitative data will be used to define appropriate measures of “male involvement” that will be used as independent predictors of reported study product adherence. Qualitative data will inform the understanding of the outcome variable of adherence in several ways. Study participants and their partners will be asked and probed on what factors contributed to their use and non-use of each product in an open-ended fashion. Responses will complement the quantitative findings, add new information and possibly clarify discordances in the quantitative data. Qualitative findings may inform the addition of potentially confounding variables in the multivariate model, i.e. if focus group respondents mentioned that being a vegetarian was the most important determinant of diaphragm use, the model would control for dietary preference.

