
**REFERENCES**

1. The closing visit may take place at 12 to 24 months (depending when the woman entered into the study) or at the woman’s last visit in the study, if she exits before her scheduled closing visit. [↑](#footnote-ref-2)
2. The OraQuick® rapid test (Epitope, Inc.) tests oral fluid, whole blood or serum/plasma samples for HIV. The device includes a porous pad that, after collection, is inserted into a vial containing a pre-mixed amount of developer solution. The specimen and solution flow through the testing device, and results are observable in about 20 minutes.

   c The Determine® rapid test (Abbott Laboratories) tests whole blood or serum/plasma samples for the qualitative detection of antibodies to HIV.

   d The AMPLICOR® PCR test (F. Hoffmann-La Roche Ltd.) test whole blood or serum/plasma samples by utilizing polymerase chain reaction technology and nucleic acid hybridization to detect HIV DNA. Detection of DNA has been shown to indicate presence of infection before an individual’s body has produced an antibody response (seroconversion).

   e HIV ELISA tests whole blood, serum, or plasma for antibodies to HIV by in vitro enzyme immunoassay. [↑](#footnote-ref-3)
3. [↑](#endnote-ref-2)
4. 1 World Health Organization (2004). Scaling Up Antiretroviral Therapy in Resource-Limited Settings: Treatment Guidelines for a Public Health Approach, 2003 revision. Available at <http://www.who.int/3by5/publications/documents/arv_guidelines/en/>. [↑](#endnote-ref-3)
5. 2 National Department of Health, South Africa (2004). National Antiretroviral Treatment Guideline. Available at <http://www.kznhealth.gov.za/arv/arv5.pdf>.

   [↑](#endnote-ref-4)
6. Although it is the man who must ultimately wear the condom, women’s “adherence” to condoms is a measure of how often she reports that her partner(s) used the condoms during sex with her. [↑](#footnote-ref-4)

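### Appendix 16.7: if items on the partner's part in condom use enter the male-involvement variable, part of its association with condom adherence is built in

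*Protocol*

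**What the plan says.** All references are to protocol Appendix 16.7.

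- **Exposure.** Under Study Aims, male involvement "encompasses the actions, preferences and attitudes of the primary male partner". Data source 1 lists participation among the domains of the Male Partner Involvement Form, next to the partner's "attitudes and support for condom, diaphragm and gel use".
- **Items and their role.** Frequency and Degree of Male Involvement first tabulates the proportions of women reporting that "her partner is supportive, aware of her study participation, like the products, participate in the use of products, etc". Key or composite variables are then expected to come out of that step: "These variables will be considered as independent predictors in further analysis of acceptability, adherence and biological outcomes". The section adds: "These measures are not pre-constructed, and have not yet been formally validated". Construct validity is to be judged by correlating single questions with the hypothesized outcomes.
- **Condom outcome.** The footnote to Study Aims says that a woman's adherence to condoms "is a measure of how often she reports that her partner(s) used the condoms during sex with her".
- **Acceptability outcome.** Data source 2 notes: "Questions about product acceptability contain partner factors in the list of potential responses women can choose". Primary Study Aim 2 builds acceptability from a combination of variables on three instruments, without naming them.
- **Adjustment.** Primary Study Aim 1 stratifies by arm because "women in condoms arm are more likely to have discussed study products with partner since he is more involved in using them", and adjusts for education and other possible confounders by logistic regression.

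**The concern.** A regression of adherence on involvement can be read as an effect of involvement only if the two are measured separately. For condoms they may not be. A question on whether the partner takes part in using the product, asked about condoms, comes close to asking whether he wears one, and the same woman reports how often he wears one as the outcome. An association would then appear even if partner support did nothing.

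The validity check adds to this. Questions that restate the outcome correlate with it by construction, so they would look the most valid and be the likeliest to be kept.

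Both primary aims are worded as effects of male involvement, and the power section presents greater male involvement as a potentially inexpensive intervention that could avert infections. A built-in condom association could be cited for that purpose.

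**Working it through.** **1. Can the planned adjustments remove the overlap?** Stratifying by arm compares women within an arm, where the overlapping item still restates the outcome. Adjusting for education removes what education explains in both variables; shared content is not a third variable and stays. The limitations section names misclassification of the construct, selection, self-report bias and unconsidered confounding, but not shared content.

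**2. The plan's benchmark.** The expected sample is 2500 × 0.9 − 13 = 2237, about 1118 per arm. Table 2 gives a minimum detectable reduction of 10 points at 50% high adherence and a 50:50 split. I checked this with a two-sided two-proportion test at 5% and 90% power, 1118/2 = 559 women per group:

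d = 1.96·√[p̄(1−p̄)·2/559] + 1.2816·√{[p₁(1−p₁) + p₂(1−p₂)]/559}

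With p₁ = 0.500, p₂ = 0.404 and p̄ = 0.452, d = 1.96 × 0.02977 + 1.2816 × 0.02963 = 0.0583 + 0.0380 = 0.096, or 9.6 points (9.8 with continuity correction). The printed 10% is reproduced. Condom adherence is to be examined in both arms; with 2237 women the same cell is about 6.8 points.

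**3. How large could a built-in difference be?** Simulation with no true effect: 1,118 women, 50% with the outcome, involvement defined as a median split of a sum of yes/no items, one or two items correlated with the outcome and the rest unrelated to it. Item counts, overlap and inter-item correlation are all assumptions. Each cell gives the false difference in points and the rejection rate of a two-sided 5% test.

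| Overlapping items (correlation with outcome) | Items mutually uncorrelated | Latent inter-item correlation 0.2 |
|---|---|---|
| 1 of 20 (0.5) | 8.8; 85% | 4.3; 31% |
| 2 of 20 (0.3) | 10.5; 94% | 4.8; 38% |
| 1 of 58 (0.5) | 5.1; 40% | 1.6; 7% |

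Hand check of the first row: SE ≈ √(2 × 0.25/559) = 0.0299. Then 8.8/2.99 = 2.94 and Φ(2.94 − 1.96) = Φ(0.98) ≈ 0.84; 4.3/2.99 = 1.44 and Φ(1.44 − 1.96) = Φ(−0.52) ≈ 0.30. Both agree with the table.

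Across repeat runs at inter-item correlation 0.2, the false difference was about 1.5 to 5.4 points, with 7% to 44% rejection at 1,118 women and 14% to 73% at 2,237.

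**4. Limits of the simulation.** Items meant to form one composite should correlate with each other, so the uncorrelated column is an upper case for these scores. The 58-item row treats every question as yes/no, whereas Data source 1 says about half have continuous scales. Scores much shorter than these would give more: an overlapping item used alone as the predictor, at correlation 0.3, gives about 29 points.

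**The case against.** The strongest reply is that nothing has been fixed yet. The quoted list belongs to a first, descriptive step; the predictors are to emerge later, and the section says that they are not yet built. The form's 58 questions are not shown, and taking part could mean reminding or agreeing rather than wearing a condom. The form is interviewer-administered at Months 3 and 12, while adherence comes from main-study data, largely by computer self-interview over three recall periods, so the two reports differ in mode and timing. Clinic attendance and permission to contact the partner are also candidate involvement measures, and neither shares this content. All of this stands. It makes the point conditional and its size unknown, but it does not answer it: participation is a named domain, the derived variables are named as predictors, and the item check runs in the wrong direction.

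A reader might infer more than this, in three ways.

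- **That the acceptability result is contaminated too.** The documents show only that partner factors are among the response options, not that they are scored into the outcome.
- **That the overlap affects every product.** For the diaphragm and gel the woman inserts the product, and no comparable overlap with her adherence is shown. None is shown for HIV or STI outcomes.
- **That the partner's liking of a product must be dropped.** Study Aims puts his preferences and attitudes inside the exposure. His liking and her acceptance are two people's attitudes, and their relation is part of what Aim 2 asks.

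**Conclusion.** The concern holds for condom adherence, conditionally: if questions on the partner's part in condom use enter the involvement variable, some of the reported association is there by construction, and the planned validity check makes their entry more likely. Fixing the item list in advance would stop data-driven selection but would not separate predictor from outcome. For acceptability the point is only a precaution about scoring.

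The size cannot be settled from the protocol. The simulated range of about 1.5 to 10 points at 1,118 women rests entirely on assumptions. Only its upper end, which needs mutually uncorrelated items, reaches the 10 points in Table 2. With moderately correlated items the false difference is smaller, but the error rate is still above the nominal 5%, and more so in the two-arm sample planned for condoms.

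This is an observational ancillary study, and the trial's HIV endpoint is untouched. The change is worth making because it is cheap.

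**What to change.** Add one paragraph to the quantitative analysis plan of Appendix 16.7:

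1. When condom adherence is the outcome, leave questions on the partner's participation in condom use out of the involvement variable.
2. Do not choose or retain questions for that variable by their correlation with condom adherence.
3. When acceptability is the outcome, leave partner-factor response options out of the acceptability score, if they would otherwise be scored.
4. Keep the partner's liking of the product in the exposure, with a sensitivity analysis that omits it.
5. Report the excluded questions descriptively.

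No new data are needed. The cost is a shorter involvement score and probably a smaller reported association.

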**Power Calculations/ Sample Size considerations for Adherence Analysis**

The MIRA sample size for the Zimbabwe site is 2500. Assuming 10% loss-to-follow-up and accounting for missing data for an additional 13 women who had already completed Month 12 before the initiation of the Male Involvement Study, the expected sample size for analysis of the association between male involvement and adherence is 2237 – 1118 in each arm of the study. The table below lists the power of the study to detect a difference in the high male involvement women vs. low male involvement, considering three ratios of high vs. low male involvement in the study population: 80/20; 60/40 and 50/50. In these calculations, three adherence level scenarios are also considered, where 90%, 70% and 50% of women with high male involvement also have “high adherence”, defined as >80% of sex acts covered by study products.

The table presents the minimum detectable relative percent difference in adherence level that the study will be able to detect with 95% confidence and 90% power between the high male involvement and low male involvement groups. In summary, the sample of 1118 women will have a high degree of power to measure relatively small differences in diaphragm and gel adherence reduction between those with high vs. low male involvement, depending on the scenarios. Condom adherence will be examined in both arms of the study, thereby doubling the available sample size and increasing the power further. In high prevalence settings, a relative “improvement” in adherence of as little as 20% between the high male involvement and low male involvement groups could have substantial public health importance and translate into thousands of infections averted, insofar as increased adherence implies a reduced probability of disease acquisition. Certainly there are other factors to consider, but willingness and ability to use disease prevention methods is a critical first step, and enhanced male involvement is a low-tech and potentially inexpensive intervention approach.

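### Male-involvement sub-study: items may be validated against the same outcomes the measure is then used to predict, which can raise the false-positive rate well above 5%

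*Protocol*

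**What the plan says.** Appendix 16.7 of the Protocol describes the exposure under Frequency and Degree of Male Involvement. It notes that no standard measure exists and that the key variables should emerge from the data. It says of them: "These measures are not pre-constructed, and have not yet been formally validated". It allows that "Composite variables may be constructed that incorporate more than one binary outcome", and then states the use: "These variables will be considered as independent predictors in further analysis of acceptability, adherence and biological outcomes". In the same paragraph the validation step reads: "tests of construct validity will be done, whereby individual questions are correlated with hypothesized outcomes in order to gauge their validity".

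The main source is the Male Partner Involvement Form: "The form has 58 questions", and "Approximately half of the responses have dichotomous yes/no responses". The same section also draws on service statistics and proxy measures, and under Primary Study Aim 1 the appendix adds that "qualitative data will be used to define appropriate measures of" male involvement. Data source 2 names women's adherence and acceptability as the sub-study's primary outcomes. For size, "the expected sample size for analysis of the association between male involvement and adherence is 2237", or 1118 in each arm.

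No independent validation criterion, separate sample or freeze of the measure before outcome linkage is described.

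**The concern.** Both primary aims ask whether involvement affects adherence and acceptability. If an item counts as a good measure of involvement because it correlates with adherence, and the resulting variable is then tested against adherence in the same women, the test partly repeats the selection. Chance correlations among many items survive into the measure and reappear as an apparent effect, with a p-value that takes no account of the search.

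The Discussion of Potential Limitations makes this reading more likely. It says the sub-study presumes that high or positive involvement goes with product use. Using that presumption to judge the items assumes what Primary Aim 1 is meant to test. The listed limitations cover misclassification, selection, self-report and confounding, but not this circularity.

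At stake is whether a positive finding on either primary aim could be told apart from item selection.

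**Working it through.** **Inputs from Appendix 16.7.** 58 items, about half yes/no (Data source 1). Sample: 2500 × 0.90 − 13 = 2237, and 2237 / 2 ≈ 1118 per arm. 95% confidence and 90% power. High adherence in 90%, 70% or 50% of women with high involvement (Power Calculations). **Assumptions, not in the document:** the item-retention rule, the number of items that are real candidates, and the correlation between items (0 to 0.5 on a latent scale).

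**Step 1. Reproduce the plan's own figures.** The two-proportion sample-size formula (two-sided 0.05, power 0.90, continuity correction, 1118 women) was solved for the detectable difference. The ranges cover both orientations of each ratio.

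| High adherence | Split 80/20: plan / recomputed | Split 60/40: plan / recomputed | Split 50/50: plan / recomputed |
|---|---|---|---|
| 90% | 9 / 8.6-8.9 | 7 / 6.9-7.0 | 7 / 6.8 |
| 70% | 12 / 11.8-11.9 | 10 / 9.6 | 10 / 9.4 |
| 50% | 13 / 12.2-12.3 | 10 / 10.0 | 10 / 9.8 |

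Table 2 is reproduced when the results are rounded up to whole points. It therefore treats involvement as a fixed exposure, with no item selection.

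**Step 2. Chance that at least one null item passes p<0.05.** For k independent items this is 1 − 0.95^k:
- k = 58: 1 − 0.95^58 = 95%
- k = 29: 77%
- k = 10: 40%

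**Step 3. Null simulation.** Each run had 1118 women, 70% high adherence unrelated to any item, and binary items with latent correlation 0 to 0.5. The selected items were summed and the sum was tested at two-sided 5% in the same women. There were 800 runs per setting, with Monte Carlo error up to about 3.5 points.

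| How items are handled | 58 items | 29 items | 10 items |
|---|---|---|---|
| Kept at p<0.05, either direction | 83-95% | 63-79% | 34-41% |
| Kept at p<0.05, hypothesised direction only | 45-79% | 32-54% | 19-23% |
| Kept at p<0.05 on a different outcome, correlated about 0.3 with the tested one | 12-24% | 10-13% | about 5% |

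The upper end of each range generally belongs to items with little correlation, the lower end to strongly correlated items. Three comparators, across all item counts:
- all items kept: 4-6%
- only items significantly in the wrong direction dropped: 2-6%
- items selected in one half of the women and tested in the other: 1-5%

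A separate simulation with half the items yes/no, 1,500 runs per setting and either-direction selection from 58 items gave 0.946, 0.945, 0.917 and 0.870 for correlations 0, 0.1, 0.2 and 0.3. This agrees with the first row.

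**Step 4. Price of a split sample.** Half of 1118 is 559. The Step 1 formula with 559 women gives detectable differences of about 10-13.5 points (90% row), 13.5-17 (70% row) and 14-17 (50% row). Table 2 states 7-9, 10-12 and 10-13.

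**The case against.** The strongest reply is that the selection step is not written down. The plan says items will be correlated with hypothesised outcomes to gauge validity. It does not name those outcomes, gives no rule for keeping, dropping or weighting items, and calls composites only possible. Other sources also define the measure: tabulations of the form, women's own descriptions, service statistics and contact permissions. Checking questions against expected correlates is an ordinary part of construct validation. The text also calls itself a summary, so some detail may sit elsewhere.

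Most of this stands as a limit on size. A reader might infer that the sub-study would almost always find an association where none exists. The document does not support that. Rates near 95% need all 58 questions as candidates, little correlation between them, and selection in either direction on the same outcome. If no items are selected on the outcome, the error rate stays near 5%. The simulated test is also an unadjusted one on a summed score, whereas the plan is a multiple logistic regression. Only one outcome was simulated as the tested one.

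It does not remove the point. The validation step is stated, not merely left open. The only outcomes named in that paragraph are the ones to be predicted, and nothing in the text prevents selection on them.

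**Conclusion.** The concern holds in conditional form. The plan leaves the involvement measure to be built from the data, provides for judging its items by correlation with outcomes best read as the sub-study's own, and then uses the result to predict those outcomes in the same women. If items are kept or weighted on that basis, the false-positive rate for the primary aims can rise well above 5%. With 58 candidate items it is about 45-79% under selection in the hypothesised direction and 83-95% under selection in either direction. With fewer candidates, or with validation on a merely related outcome, the excess is smaller and can vanish.

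These figures rest on an assumed retention rule, an assumed number of candidate items and assumed correlations between items. That adherence and acceptability are the validation outcomes is itself an inference, though a well-supported one. The matter is confined to this ancillary study.

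**What to change.** Define and freeze the involvement variables before any link to adherence or acceptability. Base them on item content, inter-item structure, the qualitative data, and indicators the sub-study already collects: whether the partner came to the clinic (Data source 5) and whether the woman permitted contact with him (Data source 6). Amend the validation sentence so that construct validity is checked against named criteria other than the tested outcomes. The sentence need not be deleted. This changes only wording and the order of analysis, and costs no sample.

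If outcome correlations are nevertheless to select items, select in a random half of the women and test both primary aims in the other half. That keeps the error rate at or below about 5%, but the detectable differences grow to those in Step 4, so Table 2 would need restating.
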